## 2. Materials and Methods

### 2.1. Study Design

This is a multicenter, randomized, parallel-group study in older patients with a recent hospitalization for AHF and/or ACS, conducted at two study sites: IRCCS MultiMedica, Sesto San Giovanni (MI), Italy, and Istituti Clinici Scientifici Maugeri IRCCS, Cardiac Rehabilitation Unit of Bari Institute, Bari, Italy. People with AHF or ACS and ≥ 65 years old were randomized into two groups: Group (A), a multidisciplinary eHealth home-based TR program; and Group (B), which received the usual care. After a minimum of 3 and up to a maximum of 6 months, enrolled subjects underwent a new evaluation for frailty. The duration of follow-up was flexible to facilitate participation and adherence. The latest available follow-up will be considered for each individual and mixed models will be used to account for different times to follow-up in the analyses. A summary of study design is presented in Figure 1. Given the nature of the study involving an active intervention only in the group assigned the eHealth arm, the trial was not blinded, i.e., investigators performing the frailty screening both at baseline and follow-up were also involved in the development of the program. The help of a caregiver was allowed but was not mandatory to participate to the study. Caregivers were not in charge of exercise supervision.

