### 2.5. Study Procedures

Step 1. Patients were screened and recruited during hospitalization in the Cardiovascular Department of IRCCS MultiMedica (Sesto San Giovanni—MI, Italy) or Cardiac Rehabilitation Unit of IRCCS ICS Maugeri (Bari—BA, Italy). The main clinical and demographic data were collected for each patient. The day before discharge, patients performed a 6 min walk test, gave a blood sample to test for molecular biomarkers and underwent a frailty evaluation on both the EFT and SPPB scales. Depression, quality of life, cognitive status, nutritional status, and adherence to medical therapy were evaluated with adequate tools. Blood samples were collected to identify biomarkers able to identify frailty and predict its progression.

Step 2. Before discharge, all enrolled patients were randomized in a 1:1 ratio to intervention (Group A) or usual care (Group B). Group A followed a multidisciplinary home-based TR program while Group B was referred to general practitioners (GPs).

Step 3. The home-based TR program was implemented in Group A patients. Group B was referred to GPs according to usual care. During step 3, clinical outcomes and adverse events were collected.

Step 4. After at least 3 and at most 6 months of follow-up, patients underwent final evaluation; the procedures of step 1 were repeated. Study procedures are summarized in Supplementary Table S1.

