### 2.22. Data Collection and Statistical Analysis

Study data were collected in the eCRF of an electronic web-based database, where each patient is identified by a randomly assigned alphanumeric code that is center-specific.

Baseline data were analyzed through descriptive analyses. Results for the overall population and for both Groups A and B are presented. Categorical variables were presented as frequencies and percentages and compared between the two groups by Chi-square test of Fisher’s exact test. Continuous variables were summarized by mean ± standard deviation and tested for normality distribution by Kolmogorov–Smirnov test. Since all variables were not normally distributed, the non-parametric Wilcoxon–Mann–Whitney U test will be used to compare baseline variables between groups. The prevalence of frail patients in the two groups is indicated as an EFT score ≥ 3. For the planned analyses, mixed models, adjusted for unbalanced variables, will be used to account for different times to follow-up. Only people with available measures of EFT at both baseline and follow-up will be included in the analyses relative to the prevalence of frailty and EFT as a continuous variable, while only individuals with available measures of SPPB at both baseline and follow-up will be included in the analyses for this endpoint. For the other covariates, missing data will be imputed through regression models. Given the limited sample size, subgroup analyses are not planned.

All analyses were performed by using SAS Software version 9.4. Tests will be considered significant for a *p* value < 0.05.

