Relative to the composition of the groups, these are well balanced, as expected by the randomization process. The only variables not balanced are sex and the SPPB. Thus, the analyses will be adjusted for such covariates, given their known relationship with the primary outcomes [25]. Cox models and ANCOVA, both adjusted for these unbalanced variables, were used to compare the prevalence and the degree of frailty, respectively. A sensitivity analysis using propensity score matching was also performed. In the active arm of the trial, 45 people performed low-level-intensity exercises and the others underwent a high-level program. Given this limited sample, subgroup analyses are not adequately powered and cannot explore whether the intervention is more effective in people with a low SPPB score, despite the prior literature suggesting that the frailest individuals (i.e., SPPB < 10) would show greater improvement [26].

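### Frailty prevalence is given a Cox model in the Discussion and mixed models in the Methods, and Cox does not suit a status read once at a flexible 3 to 6 month visit

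*Protocol article*

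**What the plan says.** Three places in the protocol article name the analysis model.

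- Section 2.1: "The latest available follow-up will be considered for each individual and mixed models will be used to account for different times to follow-up".
- Section 2.22, for the planned analyses: "mixed models, adjusted for unbalanced variables, will be used to account for different times to follow-up". The next sentence shows that this covers both versions of the EFT endpoint, since people with EFT at baseline and follow-up "will be included in the analyses relative to the prevalence of frailty and EFT as a continuous variable". The same sentence then sets the matching rule for SPPB.
- Section 4 (Discussion): "Cox models and ANCOVA, both adjusted for these unbalanced variables, were used to compare the prevalence and the degree of frailty, respectively".

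On measurement, section 2.5 describes one post-baseline assessment: "After at least 3 and at most 6 months of follow-up, patients underwent final evaluation; the procedures of step 1 were repeated". Section 2.1 adds that "The duration of follow-up was flexible to facilitate participation and adherence". Section 2.2.1 defines frailty as EFT of 3 or more, a yes/no status. No section says what time variable a Cox model would use.

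**The concern.** The same endpoints have two sets of models: Cox and ANCOVA in one place, mixed models in two others. The tense differs as well, with the Discussion writing as if the analysis were done and section 2.22 writing of it as planned. A reader cannot tell which result will be the reported one, and an analyst could choose after seeing both.

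Cox is a poor fit for prevalence in any case. It models time to an event. Here nobody observes when a patient becomes frail or stops being frail, and nearly a third were frail at the start. The only follow-up time that the schedule supplies is the date of the final visit. If that date is the time axis, a frail patient who is seen sooner counts as an earlier event, and the comparison mixes whether patients were frail with when they were seen.

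The design leaves room for timing to differ by arm. The visit date is flexible, "the trial was not blinded, i.e., investigators performing the frailty screening both at baseline and follow-up were also involved in the development of the program", and only Group A has a programme, lasting up to 6 months (section 2.18), that could influence when the final visit is booked.

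**Working it through.** **1. The plan's own figures treat prevalence as two proportions.** Inputs from section 2.20: 21% v 34%, 80% power, alpha 5% (taken as two-sided).

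n per arm = [1.960 × √(2 × 0.275 × 0.725) + 0.842 × √(0.21 × 0.79 + 0.34 × 0.66)]² / 0.13² = (1.2377 + 0.5258)² / 0.0169 = 184.01, rounded up to 185, so 370 in total. This matches section 2.20.

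With 103 per arm (section 3): z = (0.13 × √103 − 1.2377) / 0.6247 = 0.131, so power is 55.2%. This matches the 55% in the Discussion. Neither figure involves a hazard or an event time.

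**2. What a Cox model estimates if the visit date is the time axis.** Suppose frailty status at the visit is unrelated to the visit date. The event rate at time t among those not yet seen is then (probability frail) × (rate of being visited at t). Hence

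hazard ratio = (prevalence A / prevalence B) × (visit rate A / visit rate B).

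With identical timing the second factor is 1. Otherwise timing enters the hazard ratio directly.

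**3. Size of the distortion.** The documents give no visit times by arm, so the timings below are assumptions. The number per arm is 206 × 0.78 / 2 = 80, using the plan's 22% dropout. True prevalence is 30% in both arms, and the Cox model contains arm only.

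| Assumed visit timing | Median HR | Cox rejects at 5% |
|---|---|---|
| Same in both arms, uniform over 3–6 months | 1.00 | 5% |
| Both arms span 3–6 months, means differ by 0.25 month | 0.75 | 14% |
| Both arms span 3–6 months, means differ by 0.5 month | 0.57 | 47% |
| Whole window moved by 0.5 month (3.5–6 v 3–5.5) | 0.47 | 68% |
| Whole window moved by 1 month (4–6 v 3–5), worst case | 0.17 | about 100% |

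Rows 2 and 3 use beta-distributed visit times, with Group A later on average. The table was checked by rerunning it with beta parameters summing to 2, which is uniform when the means agree. More peaked shapes gave higher rejection rates. A two-proportion test on the same data stays near 5% throughout.

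The bias can go either way. With 34% frail in both arms and Group A's window 0.5 month earlier, the HR is 2.16 and 73% of tests reject. With a true 21% v 34% and the same shift, the median HR is 1.30, the wrong direction. The formula in step 2 predicts 0.618 × 2.16 = 1.33.

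**4. Loss of power even with equal timing.** With 21% v 34% and 80 per arm, the expected numbers frail are 16.8 and 27.2. The log HR is ln(0.21/0.34) = −0.482, with SE = √(1/16.8 + 1/27.2) = 0.310. Power ≈ Φ(0.482/0.310 − 1.96) = Φ(−0.41) ≈ 34%. Simulation gives 33–34%. Comparing proportions gives 47% in simulation (45% by the formula in step 1).

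**5. The benign version.** If every patient is given the same constant time, the HR estimates a prevalence ratio and timing drops out. The model-based variance of each log prevalence is then about 1/(np) instead of (1 − p)/(np). At p = 0.30 the test statistic has SD √0.70 = 0.837 under no effect, so the rejection rate is P(|Z| > 1.96/0.837 = 2.34) ≈ 2%. Simulation also gives about 2%. The test is conservative unless a robust variance is used.

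**The case against.** The strongest reply is that the distortion is hypothetical. The article does not say that visit date is the Cox time axis. Using Cox to compare a prevalence could mean the constant-time version, which has no timing bias. Both arms share the same 3 to 6 month window, and no difference in timing is reported. All of this stands, and it is why the error rates above are conditional. It does not rescue the choice of model: the time variable is left open, and the benign version still has the wrong model-based error.

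A second reply concerns weight. Section 2.2.1 says that power for prevalence is lower than planned and can be read as making it exploratory. For the means, ANCOVA and a mixed model with a baseline and one follow-up value are close. That also stands, although the abstract still calls prevalence the primary endpoint.

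A reader might infer more than the documents support:

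- That the hazard ratio will measure scheduling instead of frailty. It would reflect both, and only if visit date is the time axis and timing differs by arm.
- That the mixed models cannot handle timing. Section 2.22 does not say how time enters, and that detail may properly sit in an analysis plan.
- That taking the latest follow-up discards earlier EFT or SPPB values. Section 2.5 describes a single final evaluation.
- That Cox is already assigned to death and hospitalisation. No section names a model for those composites.

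**Conclusion.** Two things are established. First, the model statements conflict: the Discussion disagrees with sections 2.1 and 2.22 for both prevalence and degree of frailty. Second, Cox is unsuitable for a status read once at a flexible visit, and its time variable is undefined.

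The size of the second problem depends on facts the article does not give. If visit date is the time axis, mean timing differences of 0.25 to 0.5 month raise a nominal 5% error rate to about 14–47% when both arms use the full window. The 68% and near-100% figures belong to shifts of the whole window and should be read as severe and worst cases. They rest on 80 per arm, 30% prevalence, assumed visit distributions and no covariates. With equal timing the error rate is sound, but power falls to about 34% against 47%.

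The documents do not show that timing differs by arm or that any result is biased. This is a should-fix point: prevalence may be only exploratory, but its status is not stated consistently, and the conflict over models also reaches the co-primary means.

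**What to change.** - **Prevalence.** Remove Cox from the Discussion statement. Analyse EFT of 3 or more at the final visit with logistic regression or modified Poisson regression with robust variance. Report a risk difference with 95% CI. Covariates: arm, baseline EFT, centre, sex, and months from randomisation to visit.
- **Mean EFT and SPPB.** Choose one model, ANCOVA or a mixed model, and name it identically in sections 2.1, 2.22 and 4, with the baseline value and time to visit as covariates.
- **Visit timing.** Report the distribution of months from randomisation to final visit by arm.
- **If a Cox model with constant time was intended,** say so and use a robust variance. The binary-outcome model is simpler and estimates the quantity that was powered.

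The cost is wording and reprogramming. No new data are needed. The choice should be fixed and dated before follow-up results are compared by arm. If the analyses that the Discussion describes in the past tense have already been run, state that and label them accordingly.

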### 2.7. Human Biological Sample Biomarker Collection and Analysis

The collection of samples for biomarker research is part of this study. Plasma was collected from all participants in this study at baseline and was collected at the end of follow-up.

To identify novel biomarkers able to identify frailty and predict its progression, we used plasma samples collected during the frailty evaluation to identify miRNAs and inflammatory proteins cross-sectionally associated with frailty. Such candidates are derived from an unbiased miRNOmic analysis and a focused proteomic analysis. Statistical analysis revealed which markers (and relative combinations) identify a frail status. Then, after dosing such candidate molecules in the whole cohort, we performed statistical analyses to explore if such markers are also able to predict the eventual improvement or deterioration in frailty at follow-up, after intervention.

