### 2.25. Ethical Considerations

This study was conducted in accordance with consensus ethical principles derived from international guidelines including the Declaration of Helsinki and the Council for International Organizations of Medical Sciences’ International Ethical Guidelines, applicable ICH Good Clinical Practice Guidelines, and applicable laws and regulations.

The informed consent procedure included the use of simplified explanations of the digital tools involved, supported by visual aids and step-by-step demonstrations when necessary. Participants were encouraged to ask questions, and family caregivers could be involved in the discussion to facilitate comprehension and support decision-making. To verify participant understanding prior to obtaining consent, study staff provided additional explanations when needed and confirmed that participants clearly understood the study procedures, including the digital aspects, before consent was finalized. In addition, throughout the trial, participants had access to ongoing support from the research team to address potential difficulties with the digital components of the intervention. This support aimed to minimize barriers to participation and reduce the risk of digital exclusion.

The study and its amendments were approved by the Ethics Committee of IRCCS MultiMedica and CET Lombardia 5, Prot.nr.509/24 and Prot.nr.353/25. This protocol was deposited in Zenodo and is accessible at https://zenodo.org/records/18632447 (accessed on 13 February 2026).

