## 3. Results

From May 2024 to December 2025, 589 individuals were assessed for eligibility at the two centers. Among them, 147 patients were excluded because they met the exclusion criteria: more than one third (39%) were unable to use electronic devices and 21% were clinically unstable. Among the minor reasons for exclusion were MMSE < 15 (6%) and age < 65 years (4%). Therefore, we screened 442 individuals with recent ACS and AHF who fulfilled the inclusion criteria and were considered eligible for the trial. Among those eligible, 233 declined to participate in the study while two individuals could not be enrolled because they died during hospitalization. The most common reason for declining participation in the trial was the perceived complexity of being compliant with a demanding program, or the willingness to learn how to use the dedicated eHealth platform, a motivation cited by 46% of the eligible individuals approached. Overall, 19% complained about the lack of a caregiver. The remaining 209 people were enrolled in the study and assigned to one of the two groups through randomization. Two patients assigned to the control group dropped out before completing exams or questionnaires and one subject in the intervention group died before discharge (Figure 3). We compared included subjects with the subgroup of subjects who declined to participate with complete data about age, sex and type of cardiac event. The included population was representative of the eligible individuals in terms of age and sex but patients who declined were more likely to have a diagnosis of AHF compared with included individuals (58% vs. 42%, *p* = 0.0078).

Among people undergoing randomization, 103 were assigned to the eHealth intervention group and 103 to the standard-of-care control group. The baseline demographic and clinical characteristics of the two groups are presented in Table 1 while the overall characteristics of the population with the relative number of observations for each variable are shown in Table 2. Clinical characteristics were comparable in the two groups, with the exception of sex and SPPB (Table 1). Overall, the mean (±SD) age of the patients was 77 ± 9 years, and 145 subjects (70.4%) were male. The mean BMI was 25.8. More than half of the patients had ACS (55.3%). As expected, most of the people were receiving lipid-lowering medications (77.5%), antiplatelet drugs (56.4%), and one or more anti-hypertensive medications.

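### The article reports adjusted frailty comparisons as already run, with models other than the mixed models it plans, and does not say whether follow-up data by arm had been analysed when the endpoints were re-ranked

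*Protocol article*

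**What the plan says.** **Analyses reported as done.** In the Discussion paragraph on group balance, Cox models and ANCOVA, adjusted for sex and SPPB, "were used to compare the prevalence and the degree of frailty, respectively". The next sentence reads "A sensitivity analysis using propensity score matching was also performed". Section 2.7 says of the biomarkers that "we performed statistical analyses to explore if such markers are also able to predict the eventual improvement or deterioration in frailty at follow-up".

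**Analyses reported as still to come.** Section 2.22: "For the planned analyses, mixed models, adjusted for unbalanced variables, will be used to account for different times to follow-up". Section 2.1 also puts the mixed models in the future. The sentence just before the Cox/ANCOVA statement reads "Thus, the analyses will be adjusted for such covariates". Elsewhere the Discussion treats the trial's results as not yet observed.

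**Dates.** Section 3: "From May 2024 to December 2025, 589 individuals were assessed for eligibility at the two centers". The final evaluation takes place 3 to 6 months after baseline (sections 2.1 and 2.5). The latest date in the text is the one on which the deposited protocol was consulted (section 2.25): "accessed on 13 February 2026".

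**Endpoint changes.** Section 2.2.1 describes two. Mean EFT and mean SPPB became co-primary after enrolment had begun, with no date given. Frailty prevalence became exploratory after enrolment had ended, for lack of power. The trial is open, and the staff assessing frailty had helped develop the programme (section 2.1).

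**The concern.** The Cox/ANCOVA sentence cannot describe the baseline table, whose comparisons used Mann–Whitney, chi-square and Fisher tests (section 2.22 and the note to Table 1). On its face it describes the outcome comparison between arms, in an article that reports only baseline data.

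Two things are at stake. First, Cox, ANCOVA and propensity matching do not appear in section 2.22, and the mixed models do not appear in the Discussion sentence. A reader of the final report could not tell which analysis of the co-primary endpoints was the planned one. Second, the endpoint ranking changed during an open trial in which early participants already had follow-up visits. How much weight the co-primary p-values can carry depends on whether follow-up data by arm had been analysed when each change was made. The article does not say.

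**Working it through.** **1. The two accounts side by side**

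| | Sections 2.1 and 2.22 | Discussion, group-balance paragraph |
|---|---|---|
| Status | to come | done (one sentence after saying the adjustment is to come) |
| Frailty prevalence | mixed model | Cox model |
| Degree of frailty | mixed model | ANCOVA |
| Sensitivity analysis | none named | propensity-score matching |

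Changing the tense alone would still leave two different analyses.

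Section 2.7 is different in kind. No other section expressly calls the marker analysis planned; sections 2.2.2 and 2.5 only list it as an endpoint and as a purpose of sampling. The conflict there is with the calendar.

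**2. Calendar**

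- Enrolled 1 December 2025: month 3 is about 1 March 2026.
- Enrolled 31 December 2025: month 3 is about the end of March 2026, month 6 about the end of June 2026.
- On 13 February 2026, anyone enrolled after about 13 November 2025 had not reached month 3.

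If the text was fixed near that date, follow-up of the whole cohort could not have been complete.

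**3. Share already followed up (assumption: even accrual over the 20 months May 2024 to December 2025)**

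- At the end of enrolment: past month 3, (20 − 3)/20 = 85%; past month 6, (20 − 6)/20 = 70%.
- At 13 February 2026 (month 21.4): (21.4 − 3)/20 = 92% and (21.4 − 6)/20 = 77%.

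Sections 2.4.1 and 4 say the age limit was lowered during the trial because of refusals, so accrual may have risen. As an illustration only, suppose the rate doubled after month 10, giving 10 + 20 = 30 units of accrual. At the end of enrolment the shares become (10 + 14)/30 = 80% past month 3 and (10 + 8)/30 = 60% past month 6.

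**4. Does the stated reason for demoting prevalence need outcome data?**

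Inputs: 34% v 21% and 5% alpha (section 2.20; two-sided assumed), 103 per arm (section 3). With mean proportion 0.275:

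power = Φ{[0.13·√103 − 1.96·√(2·0.275·0.725)] / √(0.34·0.66 + 0.21·0.79)}
= Φ{(1.319 − 1.238)/0.625} = Φ(0.131) = **55.2%**, against 55% in the Discussion.

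A 17-point difference at the same size gives 80.4% power, which fits the Discussion's 17-point figure. The planned 370 also reproduces (185 per arm). For mean EFT, a difference of 1.95 − 1.25 = 0.70 with SD 1.25 and 90% power needs 68 per arm, 136 in all, as stated. With the planned 22% dropout (103 × 0.78, about 80 per arm), power for prevalence falls to about 45%.

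Every input is a planning value or the enrolled number. No observed outcome is needed.

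**The case against.** The strongest reply is that this is a slip of tense. The article uses the past tense for steps that could not all have happened: Step 4 of section 2.5 and the Figure 1 legend describe the follow-up evaluation as over, and section 2.22 says all analyses were performed in SAS beside analyses still to be done. The Discussion treats results as lying ahead, and no follow-up result is shown. Incomplete follow-up fits a slip at least as well as an early analysis. The power argument needs no outcome data, and section 2.2.1 openly says that the co-primaries were added after enrolment began.

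Much of this stands, and it rules out several stronger inferences a reader might draw:

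- *That an undeclared interim look took place and the co-primary p-values are invalid.* The text allows this but does not show it. Nor does the article claim that the ranking preceded any look.
- *That the co-primaries were chosen after a look.* The addition and the demotion happened at different times. The addition is undated, is justified from literature, and may precede any analysis.
- *That section 2.7 is a comparison between arms.* It describes markers predicting change in frailty and mentions no comparison by arm.
- *That open assessment amounts to an analysis.* Staff who see individual scores have not thereby compared the arms.

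The reply does not remove the conflict of models, and it does not supply the missing statement on whether data by arm had been analysed.

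**Conclusion.** The point holds as a contradiction to be resolved. The frailty comparison is described both as done and as planned, with different models in each account, so the analysis of the co-primary endpoints is not fixed by the text. Whether outcome data by arm had been analysed is open: reproducing the 55% power supports the stated motive for the demotion but cannot show that no look occurred. Until this is stated, the ranking cannot be taken as shown to be free of outcome knowledge.

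The calendar conclusion rests on the text having been fixed near 13 February 2026. That is a repository access date, not a data cut or the date of the final text. The share followed up when enrolment closed (about 70% past month 6 and 85% past month 3) rests on even accrual and is lower if accrual rose after the age limit changed.

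**What to change.** 1. Reconcile section 2.7 and the Discussion with sections 2.1 and 2.22, so that each analysis is described once, with its true status.
2. Name one primary model for each co-primary endpoint and run it once on the complete locked data. The mixed model already stated in sections 2.1 and 2.22 would serve, with ANCOVA and propensity matching labelled as sensitivity analyses. State the model for prevalence as well.
3. Give separate dates for the addition of mean EFT and mean SPPB and for the demotion of prevalence. For each date, state whether any follow-up data by arm had been analysed.
4. If a comparison was run, declare it as an unplanned interim look with its date, data cut and endpoints. Report prevalence as the original primary endpoint and the two means as promoted during the trial.
5. Give any share of patients already followed up as an assumption, or replace it with the actual count.

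If no look occurred, the cost is a few sentences and one dated statement, which would protect the co-primary result. If one did, the trial's conclusion becomes more cautious.
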